# Neck-specific strengthening exercise compared with sham ultrasound when added to home-stretching exercise in patients with migraine: study protocol of a two-armed, parallel-groups randomized controlled trial

**DOI:** 10.1186/s12998-020-00313-w

**Published:** 2020-05-19

**Keywords:** Cervical exercises, Migraine disorders, Electromyography, Neck pain

## Abstract

**Background:**

Migraine is a highly disabling condition and pharmacological treatment is the gold standard. However, several patients have also positive responses to the application of different manual techniques and therapeutic exercises in terms of reducing the intensity and frequency of migraine attacks. Nevertheless, the effects of a neck-specific exercise program have not yet been evaluated in these patients.

**Objective:**

To determine the effectiveness of a neck-specific exercise program in reducing the intensity and frequency of migraine attacks as compared to a sham ultrasound group.

**Methods:**

A two-armed, parallel-groups randomized controlled trial with 3 months of follow-up will be conducted. 42 individuals, both genders, aged between 18 and 55 years old with a medical diagnosis of migraine will be included. The intervention group will perform a protocol consisting of exercises for strengthening the muscles of the cervical spine. Participants within the sham ultrasound group will receive detuned ultrasound therapy in the upper trapezius muscle. Both groups will receive a weekly session for 8 weeks. The efficacy of each intervention will be measured by the frequency and intensity of migraine at a 3-months follow-up.

**Trial registration:**

This study was registered under access code RBT-8gfv5j in the *Registro Brasileiro de Ensaios Clínicos* (ReBEC) in November 28, 2016.

**Conclusion:**

This study will aim to determine the efficacy of a neck-specific exercise program in reducing the frequency and intensity of migraine attacks. If the results show that a neck-specific exercise program is effective in reducing the frequency and intensity of migraine attacks, therapists will have a low cost and easily applicable tool to treat migraine.

## Introduction

Migraine is classified as a chronic [1] and disabling disease [2] characterized by recurrent headache attacks lasting from 4 to 72 h, with a unilateral location and pulsating quality. Migraine attacks range from a moderate to severe intensity that increases with daily routine, physical activity, and can be accompanied by nausea and/or photophobia and phonophobia [3]. In addition to these features, neck pain is quite common [4] and is associated with a worse prognosis for the disease [5].

Pharmacologic treatment is currently the gold standard for migraine management [6]. However, a multidisciplinary approach is also recommended [7] and manual techniques and therapeutic exercises may be valuable adjunct treatments as they help to reduce symptoms, prevent migraine attacks [8], and result in a relevant clinical reduction of the frequency and intensity of migraine attacks while increasing patient satisfaction with the treatment [9].

Among the various manual technique interventions, aerobic exercises in combination with physical and psychological interventions result in a reduction in the duration of migraine attacks [8]. It is known that aerobic exercises were as effective in reducing the frequency of migraine attacks as standard pharmacological treatment with topiramate and tricyclics [10]. In addition, manual therapy interventions targeting the craniocervical region have also demonstrated beneficial results, such as improvement in the quality of life, reduction of pain intensity, reduction in related disability, and a reduced frequency of migraine attacks [11–14]. However, despite evidence showing that different manual techniques and therapeutic exercises in the craniocervical region are effective in migraine management [8–14], to date, the effects of cervical muscle strengthening exercises on this population are unknown [15].

In individuals suffering from neck pain, neck-specific exercises have been shown to be effective in reducing neck pain [16–18], improving performance in the craniocervical flexion test [16], and strengthening the cervical deep flexor and extensor muscles [19–21]. Considering that individuals with migraine also exhibit cervical dysfunctions [8, 22–27], we believe that, similar to what has been observed in subjects with neck pain [28], individuals with migraine may also benefit from these types of exercises. The hypothesis of this study is that the strengthening exercises have greater improvement than sham ultrasound in reducing migraine frequency and intensity when practiced in combination with home stretching exercises.

### Primary and secondary objectives

The primary objective of the current study is to determine the efficacy of a neck-specific strengthening exercise program in reducing the frequency and intensity of migraine attacks in subjects with migraine, compared with the sham ultrasound group. We also intend to determine whether craniocervical exercises influence the intensity of migraine attacks, migraine-related disability, concomitant neck pain, and the quantitative variables, including neck range of movement, pressure pain threshold, motor control of the deep flexor muscles, neck muscle strength, and resistance of cervical musculature.

## Methods

### Design

A two-armed, parallel-group randomized controlled trial designed according to the CONSORT guidelines [29].

### Ethics approval

The protocol has been approved by the local ethics committee (no. 6862/2016) and registered under access code RBR-8gfv5j in the Registro Brasileiro de Ensaios Clínicos (ReBEC).

### Setting of the study

The study protocol described here was designed according to the recommendations of SPIRIT [30]. Given that this protocol will be applied in individuals with migraine, our selection of criteria for inclusion, exclusion, and choice of outcomes was also guided by the suggestions of the International Headache Society [31].

The study will be conducted in a single center, located at the University of São Paulo, in Ribeirão Preto, Brazil, and will include three main researchers, two of whom will be responsible for data collection and one of whom will be responsible for the treatment in both groups. In addition, a team of four more researchers will be responsible for screening volunteers.

### Participants

Volunteers for the study will be included if they are between 18 and 55 years old, are of either sex, have been diagnosed with migraine according to the third edition of the International Classification of Headache [3], and have exhibited at least 3 days with migraine attacks in the previous month [31]. The inclusion and exclusion criteria are fully described in Table 1.

**Table 1 Tab1:** Inclusion and exclusion criteria

Inclusion	Exclusion
18–55 years old	Another type of headache
Both sexes	Medication overuse headache
Diagnosis of migraine	History of trauma in the cervical and/or face
Minimum of 3 days with migraine/month	Diagnosis of hernia or disk degeneration in the cervical region
	Systemic diseases^a^
	Pregnancy
	Anesthetic block in the three months prior to the selection process
	Have received manual techniques or therapeutic exercises in the last year in craniocervical region

^a^e.g.: fibromyalgia, diabetes, peripheral neuropathies

### Recruitment

Volunteers will be recruited from the local population by announcements. The study will be released on social media (Facebook®, Instagram®, and local university radio), and those who apply will be referred to a neurologist with at least 5 years of experience in the diagnosis of headache and migraine, who will perform the migraine diagnosis. Those participants who meet all eligibility criteria will be invited to participate in the trial.

### Study schedule

#### Screening

A prescreening will be conducted among individuals who expressed an interest in the study on social media. The basic criteria of their migraine will be queried (e.g., location, intensity, and type of headache), and those who apparently fit the characteristics of migraine will be referred to the neurologists. After confirming the diagnosis of migraine and the inclusion criteria, the volunteer will be invited to participate in the study. Those who accept the invitation will receive all pertinent information about the study and begin to fill a paper headache diary [9]. After 30 days, the volunteer will undergo evaluation 1, which will consist of the application of questionnaires and a physical examination, and at the end of evaluation 1 randomization will occur. Depending on patient availability, treatment will begin in the next few days. Follow-up will occur 1, 2, and 3 months after the end of treatment.

The study design, which covers the screening, evaluation, intervention, and follow-up procedures is summarized in Fig. 1.

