#### Randomization and blinding

Participant allocation will be determined in sequential order, randomized by Excel®. Blinding will be ensured by giving the participant a brown and opaque envelope containing their group assignment, which will be opened in front of each participant. The envelopes will be prepared in advance by an independent researcher; envelopes will be opened in front of each participant. A single therapist, blinded to the results obtained during evaluations, will be responsible for all the interventions in both groups. Similarly, the therapist responsible for data collection will be blinded to the treatment allocation group (intervention or sham ultrasound).

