### Statistical analysis

All statistical analyses will be performed by a professional statistician and they will be blinded to the allocation groups. An intention-to-treat analysis will be performed in order to verify the effect on the outcomes. Intention-to-treat analysis is the most indicated statistical analysis method in randomized clinical trials because it allows verification of the real efficacy of the intervention, and avoids an overly optimistic estimate that may result from removal of the non-adherent volunteers [51]. Mixed linear regression models will be performed for the primary and secondary outcomes to estimate between-group and within-group comparisons. “Time” and “group” will be considered as fixed effects and participants as a random effect (random intercept model). Baseline will be used as a covariate and the term “interaction time by group” will be included in the model to evaluate the interaction effect of differences between groups at each follow-up and within-group differences over time. Additionally, post hoc Bonferroni correction will be performed for group comparisons at each follow-up in the case of a significant “time” X “group” interaction.

In addition, to determine the clinical relevance of between-groups differences, Minimal Clinically Important Difference (MCID) calculations will be performed for the variables that do not have the MCID described in the literature, and the Effect Size (ES) will be calculated based on the distribution methods. Differences will be considered clinically relevant when they overcome the MID combined with an ES > 0.4, following the criteria suggested by Armijo-Olivo et al. [52]

For the missing data, as recommended by CONSORT [29], imputation occurs through a mixed effect regression model*.*

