### Sample size

A sample size of 21 individuals on each group was the result of a calculation in which a level a significance (α) of 0.025 was adopted, with a power of 80%, a between-groups difference to be detected of 3.3 (SD = 3.1) days of headaches per month, and considering a loss of 20% at follow-up. The mean and standard deviation used in the sample size calculation were based on the reduction of the frequency of a gold standard pharmacologic treatment group for migraine management from a previous clinical trial [9]. For the primary outcome “headache intensity”, adopting the same parameters as the previous calculation, a sample size of 20 would be necessary to detect a between-groups difference of 1.52 (SD = 1.37) in the NPS, based on data from 4-week pharmacological treatment [53].

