### Strengths and weaknesses of the study

Strengths of the study include the design and the novelty of investigating whether a neck-specific strengthening exercise program might reduce the frequency and intensity of migraine attacks. The gold-standard treatment for migraine is pharmacological. However, manual techniques and therapeutic exercises have shown satisfactory results in reducing migraine attacks and improving quality of life. We recognize that the application of an exercise program alone is a limitation of this study, because it may not represent common clinical practice. However, from a scientific perspective, the effects of this protocol should be specifically determined before combining it with other interventions.

We can cite as other limitations: no long-term follow-up, attention bias from the differences between groups in the time spent with a therapist, long home exercise assignments, only partial blinding of participants (they can distinguish treatments, but they are blinded to sham ultrasound), the estimates of the mean and standard deviation used in the sample size calculation came from a different study population, and adverse events will not be collected.

Finally, although we will attempt to make the number of meetings the same when inserting the sham group with ultrasound, patients who will receive this placebo may have the feeling of greater attention because they will receive a type of hands on therapy. In addition, patients in the sham group may have a greater perception of improvement than the intervention group. However, implementing a placebo group that received another type of exercise would also be controversial because the effects of non-specific exercises on migraine are already known.

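### Participants appear to learn their arm some days before the first session, which leaves a short, avoidable window for arm-related non-starting

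*Protocol article*

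**What the plan says.** Under Screening, the Protocol article has volunteers keep a headache diary for 30 days and then attend evaluation 1 (questionnaires and physical examination). It continues: "at the end of evaluation 1 randomization will occur. Depending on patient availability, treatment will begin in the next few days".

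Under Randomization and blinding, allocation is disclosed by "giving the participant a brown and opaque envelope containing their group assignment, which will be opened in front of each participant". The envelopes are prepared in advance by an independent researcher. The section does not say at which moment, or by whom, they are opened. One therapist delivers all sessions in both arms, and the data collector is to be blind to allocation.

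Under Strengths and weaknesses of the study, the authors list "only partial blinding of participants (they can distinguish treatments, but they are blinded to sham ultrasound" as a limitation. They also list the length of the home exercise assignments.

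Under Statistical analysis, "An intention-to-treat analysis will be performed in order to verify the effect on the outcomes", because this "avoids an overly optimistic estimate that may result from removal of the non-adherent volunteers". For missing data, "imputation occurs through a mixed effect regression model". Sample size allows for 20% loss at follow-up. Nothing in the article addresses withdrawal between allocation and the first session.

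**The concern.** Taken together, these sections imply that a participant learns a recognisable allocation before attending any session. The arms then ask different things of people at home. Both do stretching, but the exercise arm adds strengthening exercises twice daily, while the comparator arm has a stretching booklet and passive ultrasound at the weekly visit. A participant who is put off by the assignment, or disappointed by it, can simply not come to session 1.

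Two consequences are possible, and they should be kept apart:

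- A non-starter who still returns diaries is analysed in the assigned arm without having had the treatment, so the estimated difference moves towards zero.
- A non-starter who leaves has no outcome after baseline and enters only through imputation. If leaving depends on the arm and on something not recorded, such as motivation, imputation from the recorded data cannot be relied on to correct for it. The 20% allowance protects the number analysed, not the balance between arms.

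Nothing visible in the design requires allocation at evaluation 1. Baseline measurement is complete by then, and every participant who starts is seen by the same therapist at session 1.

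**Working it through.** **1. The plan's own sample size.** Inputs from Sample size: "level a significance (α) of 0.025 was adopted", power 80%, difference 3.3 days per month, SD 3.1, loss 20%. The article does not say whether alpha is one- or two-sided; two-sided is assumed because it reproduces the stated figure.

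- n per arm = 2 × (z₀.₉₈₇₅ + z₀.₈₀)² × (SD/difference)² = 2 × (2.241 + 0.842)² × (3.1/3.3)² = 16.8, rounded up to 17.
- With 20% loss: 17 × 1.2 = 20.4, giving 21 (the stated figure); 17/0.8 = 21.25, giving 22.
- Intensity (1.52, SD 1.37) gives 16, and 16/0.8 = 20, which is the stated figure.

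The plan's numbers are therefore not in dispute here.

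**2. Non-starters who are still measured.** Assume that k of the 21 in the exercise arm never start, gain none of the effect and return their diaries. The expected difference is 3.3 × (1 − k/21):

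| k | Expected difference (days) |
|---|---|
| 0 | 3.30 |
| 1 | 3.3 × 20/21 = 3.14 |
| 2 | 3.3 × 19/21 = 2.99 |
| 4 | 3.3 × 17/21 = 2.67 |

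The range 0 to 4 is an assumption, as the article gives no rate.

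Power for a share w of such non-starters, with effect 3.3 × (1 − w), SD 3.1, two-sided alpha 0.025 and the normal approximation:

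| w (assumed) | 21 per arm measured | 17 per arm measured |
|---|---|---|
| 0% | 88.6% | 80.6% |
| 5% | 85.0% | 76.0% |
| 10% | 80.6% | 70.9% |
| 15% | 75.5% | 65.4% |
| 20% | 69.8% | 59.5% |

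The right-hand column applies if the planned 20% loss also occurs (21 × 0.8 = 16.8, taken as 17).

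**3. Non-starters who leave.** These are missing data, not diluted data. If they make up the planned loss and nothing else is lost, 17 per arm gives 80.6% power and 16 gives 77.9%, so precision is about what was planned.

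The remaining issue is bias. If m of 21 leave one arm only, and their unobserved mean differs by δ from that of those who stay, after whatever the imputation explains, that arm's mean is off by (m/21) × δ. Taking δ as large as one SD (3.1 days, an assumption), one leaver shifts it by 3.1/21 = 0.15 days and four by 4 × 3.1/21 = 0.59 days. Equal losses of the same kind in both arms would cancel.

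**4. The timing.** Screening dates randomisation to the end of evaluation 1. Randomization and blinding describes no allocation step other than the envelope. Disclosure at evaluation 1 is therefore the natural reading, but it is an inference: the moment of opening is not written down, and the schedule figure is not visible here.

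**The case against.** Randomising after baseline and starting within days is ordinary practice, and the article neither contradicts itself nor misstates a figure here. Four stronger readings are tempting, and the article supports none of them.

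- *Keeping untreated non-starters in the analysis is an error.* It is not. It is what intention-to-treat requires, and the article gives the right reason for it. Excluding them would be the biased choice.
- *The gap is unlimited.* No maximum is set, but the text describes a start within a few days, with availability deciding which day.
- *The trial will lose the effect or power shown above.* The dilution figures apply only to non-starters who gain nothing and are still measured. Someone who withdraws altogether returns no diary and falls under imputation and the 20% allowance. With all 21 per arm measured, power is still 80.6% at 10% non-starters.
- *Opening the envelope later would remove the problem.* A participant who learns the arm at session 1 can still decline or fail to return, and the burden of home exercise acts over all eight weeks.

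It is also fair to say that participants are informed about the study, keep a diary for 30 days and complete a full assessment before randomisation. That filters out the less committed. All of this limits the size of the concern. It does not remove the point that the window after disclosure can be avoided at little cost.

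**Conclusion.** The concern holds as a modest design improvement. As the article reads, allocation is disclosed some days before the first session in a trial where participants can distinguish the arms, and that permits arm-related non-starting that need not be permitted.

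Each non-starter in the exercise arm is 4.8% of that arm and dilutes the effect by that share if still measured and wholly unaffected; each one who leaves adds missing data that may differ by arm. How many there would be is unknown and probably small. The conclusion rests on the inference that the envelope is opened at evaluation 1, and the illustrative sizes rest on assumed counts.

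**What to change.** Amend Screening and Randomization and blinding in the Protocol article as follows:

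- After evaluation 1 and before allocation, session 1 is booked for every eligible participant.
- The next sealed, opaque, sequentially numbered envelope is opened with the participant only on attendance at session 1. The allocated intervention begins at once, and that date is recorded as the randomisation date.
- Anyone who does not attend is not randomised, and the envelope stays sealed for the next participant.
- The text names who opens the envelope. Preparation stays with the independent researcher, so that the sequence remains concealed.

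Failure to attend session 1 then cannot depend on the arm, and the intention-to-treat analysis is unchanged. Disclosure also moves away from the assessment visit, which helps to keep the data collector blind. Loss after session 1 is not affected.

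The change needs no new visit, staff or analysis. Its costs are a few full evaluations of people who are never randomised, an interval from baseline to randomisation that is a few days longer (the interval from baseline to treatment stays as it is), and an envelope procedure to be written and logged.

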**Fig. 1 Fig1:**
[figure not shown]
Study schedule summary *NDI* Neck Disability Index; *MIDAS* Migraine Disability Assessment; *TAMPA* Tampa Scale for Kinesiophobia; *PSFS* Patient-specific Functional Scale; *ASC-12* 12 item Allodynia Symptom Checklist; *CROM* Cervical range of motion; *PPT* pressure pain threshold; *CCFT* craniocervical flexion test; *MIVC* maximal isometric voluntary contraction; *EMG* electromyography

#### Randomization and blinding

Participant allocation will be determined in sequential order, randomized by Excel®. Blinding will be ensured by giving the participant a brown and opaque envelope containing their group assignment, which will be opened in front of each participant. The envelopes will be prepared in advance by an independent researcher; envelopes will be opened in front of each participant. A single therapist, blinded to the results obtained during evaluations, will be responsible for all the interventions in both groups. Similarly, the therapist responsible for data collection will be blinded to the treatment allocation group (intervention or sham ultrasound).

